### Eligibility criteria

Participants will be eligible for the study if they are aged 12 years or older with a physician‑confirmed diagnosis of asthma, are currently prescribed at least one daily controller medication, have been on asthma medication for a minimum of three months prior to enrollment, are able to read and understand the educational materials (if the patient cannot read, a literate caregiver may assist, and all content will also be explained verbally), have access to a telephone for follow‑up calls and text messages, and are willing to provide written informed consent. Participants will be excluded if they are not currently prescribed a daily controller medication; are unable to read and have no literate caregiver to assist; have no telephone access; have a cognitive or severe psychiatric condition that impairs their ability to understand the study or provide consent; or are unable to communicate effectively in Tigrinya or Amharic.

### Randomization

All participants who provide written informed consent and meet the eligibility criteria will be randomly assigned in a 1:1 ratio to either the intervention group or the control group. A block randomization method will be employed using a computer‑generated random number sequence prepared by an independent investigator who is not involved in participant recruitment or intervention delivery. The allocation sequence will be concealed from the research team enrolling participants using sequentially numbered, opaque, sealed envelopes.

## Intervention

### Intervention group

Participants assigned to the intervention group will receive standard care augmented by a structured, multi‑component intervention delivered by trained post baccalaureate Doctor of Pharmacy interns under the supervision of a clinical pharmacy specialist. The intervention will begin on the day of enrollment with a 30‑minute, one‑on‑one, face‑to‑face session. This session will cover comprehensive asthma education, including common triggers and actions to take during an exacerbation, the importance of daily adherence to controller medications, and hands‑on inhaler technique training using a placebo device and the teach‑back method for immediate corrective feedback. It will also include managing medication side effects and developing personalized adherence strategies. Participants will receive illustrated educational pamphlets in the local language (Tigrigna). The initial session will be reinforced by a 2‑minute follow‑up phone call in the first month to assess their general condition, check their adherence status, and address any questions or challenges they encounter, as well as a standardized motivational text message (SMS) in the second month to encourage sustained adherence to their medications and follow‑up. Participants will also be informed that they may initiate contact with the study team at any time to address questions or concerns.

### Control group

Participants assigned to the control group will receive standard routine care. They will not receive any structured education or counseling from the research pharmacist or study team.

### Data collection

Data will be collected at baseline and after the three‑month follow‑up period using a structured questionnaire. The three‑month follow‑up assessment will be conducted during a scheduled clinic appointment at the hospital. At this visit, the same blinded data collectors will re‑administer the full questionnaire. The tool will capture socio‑demographic information, clinical characteristics, and the study outcomes using the following instruments: the General Medication Adherence Scale (GMAS) [39], the Asthma Control Test (ACT) [40], a knowledge assessment questionnaire adopted from previous literature [1,41,42], and a standardized inhaler technique checklist adapted from National Institutes of Health (NIH) guidelines [21]. The original English versions of these instruments will be translated into the local language (Tigrigna) by an independent bilingual translator. This version will be reviewed for content and face validity by an expert panel of senior clinical pharmacists, a pharmacologist, and a chest unit physician. To ensure conceptual accuracy, the Tigrinya version will be back‑translated into English by a different translator, with all discrepancies reconciled. Trained data collectors, blinded to participant group allocation, will administer the tool through face‑to‑face interviews. Inhaler technique will be assessed by direct observation of the participant’s demonstration using their own device, scored against a standardized checklist.

### Statistical analysis

Statistical analysis will be performed using SPSS version 28.0. Descriptive statistics will summarize participant characteristics: categorical variables as frequencies and percentages, continuous variables as means with standard deviations or medians with interquartile ranges. The primary analysis will follow the intention‑to‑treat principle, analyzing all participants according to their original randomized group regardless of whether they completed the intervention. For the primary outcome (dichotomized medication adherence), the proportion of adherent participants will be compared between groups using the chi‑square test. Within‑group changes from baseline to follow‑up will be tested using McNemar test. Between‑group differences at follow‑up will be analyzed using Pearson’s chi‑square test (or Fisher’s exact test when expected cell counts are < 5). For continuous variables with skewed, the Mann‑Whitney U test will be used. Multivariable binary logistic regression will be employed to identify factors associated with poor medication knowledge, medication non‑adherence, and uncontrolled asthma, with the intervention group as the main independent variable adjusted for potential con-founders (age, sex, education, income, Comorbidities, exacerbation history, and smoking status). Effect sizes will be reported as adjusted odds ratios with 95% confidence intervals. Subgroup analyses will be performed to explore whether the intervention effect differs across patient characteristics (age, gender, education, occupation, income, GINA step, comorbidity, exacerbation history) using logistic regression with interaction terms; p‑values for interaction will be reported. Missing data will be handled by complete case analysis if the proportion is low (<5%); otherwise, multiple imputation will be considered. A p‑value < 0.05 will be considered statistically significant.

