**Methods:**

A single‑blind, parallel‑group randomized controlled trial will be conducted. All eligible adult asthma patients on active follow‑up at the chest clinic of Ayder Comprehensive Specialized Hospital will be included. Participants will be randomly assigned via a computer‑generated sequence to an intervention group (structured pharmacist‑led education using teach‑back, illustrated pamphlets, a follow‑up phone call and SMS) or a control group (routine care). Outcome assessors will be blinded to group allocation. Outcomes will be measured at baseline and after three months, including medication adherence (GMAS), asthma control (ACT), medication knowledge, correct inhaler technique, and domain‑specific adherence barriers. Data will be analyzed using intention‑to‑treat with multivariable binary logistic regression, chi‑square tests, independent T-test, McNemar test, Mann‑Whitney U test, and Fisher’s exact test where appropriate. Subgroup analyses will be performed to explore whether the intervention effect differs across patient characteristics. A p‑value < 0.05 will be considered statistically significant, with 95% confidence intervals reported.

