### Sample size

A formal a priori sample size calculation was not performed because the study aimed to include the entire eligible population. The final sample consisted of 131 adult asthma patients. A post‑hoc power analysis was conducted using parameters derived from published studies in low‑income countries. Based on a meta‑analysis of adherence in Ethiopian asthmatic patients, the pooled baseline adherence is approximately 40% [4]. A clinically meaningful improvement of 20 percentage points (to 60%) was considered, consistent with pharmacist‑led intervention studies in Nigeria [38] and Vietnam [1]. Using a two‑proportion test with α = 0.05 (two‑sided) and a sample size of 131 (approximately 65 per group), the study achieves 80% power to detect an absolute difference of 20 percentage points.

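### Within-arm McNemar tests are planned at p<0.05 without a descriptive label, while the between-arm analyses leave out the baseline value of the outcome

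*Protocol article*

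**What the plan says.** In the protocol article, Statistical analysis, within-group change from baseline to follow-up "will be tested using McNemar test". The sentence names no outcome. The Abstract (Methods) also lists "independent T-test, McNemar test" among the analysis methods. One significance rule covers everything: a p-value below "0.05 will be considered statistically significant". The within-group tests are neither exempted from it nor called descriptive.

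The randomised comparison is specified separately. "For the primary outcome (dichotomized medication adherence") the plan states that "the proportion of adherent participants will be compared between groups using the chi"-square test, under intention-to-treat. Follow-up differences between groups are tested with Pearson's chi-square or Fisher's exact test. The logistic models have randomised group as the main independent variable, and "Effect sizes will be reported as adjusted odds ratios with 95% confidence intervals". The adjustment list is age, sex, education, income, comorbidities, exacerbation history and smoking status. The Outcome measures section says that every outcome is assessed at baseline as well as at three months, yet no baseline outcome value is on that list.

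**The concern.** A change within one arm is not an estimate of what randomisation was meant to isolate. It adds any intervention effect to time trend, regression to the mean and the effect of being interviewed a second time. All three are plausible here. Adherence is self-reported, the same data collectors repeat the full questionnaire face to face, and patients enter the trial while attending a clinic.

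If both arms improve for these shared reasons, each McNemar test has some power to detect the shared rise. By chance one arm can cross 0.05 while the other does not. A table showing significant improvement under the intervention and none under control then looks like evidence of benefit, although it is not a test of the difference between arms.

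The second half of the concern is where the baseline data go. The baseline value of the same outcome is usually one of the stronger predictors of its follow-up value. The plan uses it in the within-arm tests and leaves it out of the between-arm analyses, where it could add precision and correct chance imbalance.

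**Working it through.** **The plan's own figure.** The plan gives no operating figure for the McNemar tests. The nearest figure is the 80% power in Sample size, for 40% against 60% with about 65 per arm. The pooled normal formula gives Φ[(0.20·√65 − 1.96·√(2·0.5·0.5)) / √(0.24 + 0.24)] = Φ[(1.612 − 1.386)/0.693] = Φ(0.327) = 62.8%. The 80% does not reproduce. That is a separate finding, and nothing below depends on it.

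**Inputs from the protocol.** Baseline adherence: "pooled baseline adherence is approximately 40" per cent. Patients: 131, about 65 per group, 1:1. Alpha: 0.05, two-sided.

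**Assumed inputs, not in the documents.** The same true change in both arms (0 to +20 points), hence no intervention effect. A latent (bivariate normal threshold) correlation ρ between a patient's baseline and follow-up status, from 0 to 0.7.

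**Step 1: transition probabilities.** With follow-up proportion p₁, the probability of being adherent both times is p₁₁ = Φ₂(Φ⁻¹(0.40), Φ⁻¹(p₁); ρ). The probability of moving to adherent is p₁ − p₁₁, and of moving away is 0.40 − p₁₁. For p₁ = 0.50 and ρ = 0.5, p₁₁ = 0.280, giving 0.220 and 0.120.

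**Step 2: one arm.** Enumerate the exact McNemar test over all discordant counts for n = 65. Let a be the probability that p<0.05 in either direction, and u the part of a that is an improvement. In the example, a = 0.213 and u is almost the same.

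**Step 3: two independent arms with the same true change.** P(significant improvement in the intervention arm only) = u(1 − a). In the example, 0.212 × 0.787 = 0.167.

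Results, in per cent of trials with no intervention effect:

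| Change in both arms | ρ = 0 | ρ = 0.3 | ρ = 0.5 | ρ = 0.7 |
|---|---|---|---|---|
| none (40% to 40%) | 1.5 | 1.4 | 1.4 | 1.4 |
| +5 points | 5.3 | 5.8 | 6.4 | 7.4 |
| +10 points | 13.1 | 14.8 | 16.7 | 19.8 |
| +15 points | 22.0 | 23.8 | 24.8 | 24.5 |
| +20 points | 24.7 | 23.1 | 20.1 | 13.8 |

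A 65/66 split moves these by less than one percentage point. The figures fall again at +20 points with high ρ because both arms then tend to be significant together.

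**Step 4: the planned between-arm test.** In simulation with no intervention effect (200,000 runs, 65 per arm), for no common change and for common rises of 10 to 20 points, the between-group chi-square test rejects in 4.4–5.3% of trials, about half of that in each direction. The primary error rate is therefore intact. At ρ = 0.5 and common rises of 10, 15 and 20 points, the combination of improvement significant in the intervention arm only and a non-significant between-arm test occurs in about 15%, 23% and 18% of trials (20,000 runs).

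**The case against.** The strongest reply is that the plan does not commit the error. A reader might infer that benefit will be claimed when McNemar is significant in one arm and not in the other. No sentence in the article plans that comparison. The primary test, the follow-up tests and the effect sizes are all between-arm, and subgroup claims use interaction terms rather than separate tests within subgroups. This stands: the main inference does not rest on McNemar.

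A second reply is that one-arm-only significance is not frequent in itself. This also stands. It becomes common only if both arms improve, and the documents give no such figure. "A clinically meaningful improvement of 20 percentage points (to 60%) was considered", but that is the gain targeted for the intervention, not a control-arm trend. With no common change the rate is about 1%, below the roughly 2.5% error of the between-arm test in favour of the intervention.

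A third reply is that McNemar validly answers whether an arm changed, and that an analysis plan not shown here may call these tests descriptive. The first part is true, but whether an arm changed is not the trial's question. On the second, the article says *tested*, applies the general threshold and lists McNemar beside the between-group tests. It also spells out the covariates without the baseline outcome. Those are stated choices, not details left open.

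**Conclusion.** The point holds in a limited form. The plan attaches significance tests to a contrast that does not estimate the randomised effect, does not label them descriptive, and keeps the baseline outcome out of the analyses that do estimate it. The primary analysis remains valid and its error stays near 5%.

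The size of the risk depends on an unknown shared improvement. A false impression of benefit from the intervention arm alone arises in about 1% of null trials with no common change, 5–7% at +5 points and 13–25% at +10 to +20 points. These figures rest on 40% baseline adherence, about 65 per arm, exact McNemar tests and an assumed latent correlation of 0 to 0.7. They describe how often the pattern appears. It becomes a false claim only if someone reads the pattern as a treatment effect in place of the planned between-arm test. The documents do not support saying that the authors intend this.

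**What to change.** Make three changes in Statistical analysis, and match the Abstract to them.

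1. Report within-arm change descriptively: the number and percentage moving to and from adherent (and likewise for the other binary outcomes), with no claim of significance.
2. Add the baseline value of each outcome to its between-arm logistic model: baseline adherence to the adherence model, baseline control to the control model, baseline knowledge to the knowledge model.
3. State that conclusions about effectiveness rest only on the between-arm estimates.

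The cost is small. The within-arm p-values are lost, and each model gains one covariate, on top of randomised group and the seven already listed. The adjusted odds ratio then becomes conditional on baseline status as well, which the report should say. No new data are needed. The Trial status section says that analysis has not begun and no results have been examined, so the change can still be made before anyone has seen outcomes.

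### The meaningful effect is defined in percentage points, but the one effect size named is an adjusted odds ratio, and no confidence interval for the difference is planned

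*Protocol article*

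**What the plan says.** In the Protocol article, the Sample size section sets the effect of interest on the absolute scale: "A clinically meaningful improvement of 20 percentage points (to 60%) was considered", starting from about 40% adherence. It states power on the same scale, saying that "the study achieves 80% power to detect an absolute difference of 20 percentage points". The same section says that no a priori calculation was made, because the whole eligible population was to be enrolled, and that the power analysis is post hoc.

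The Statistical analysis section gives the primary comparison: "For the primary outcome (dichotomized medication adherence), the proportion of adherent participants will be compared between groups" by a chi-square test. It then describes a multivariable logistic regression for poor knowledge, non-adherence and uncontrolled asthma. The group is the main independent variable, and the model adjusts for seven characteristics: age, sex, education, income, comorbidities, exacerbation history and smoking. Directly after that comes the one sentence on effect measures: "Effect sizes will be reported as adjusted odds ratios with 95% confidence intervals".

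The Outcome measures section has GMAS recorded at baseline as well as at three months. Baseline GMAS is not in the covariate list. The Abstract adds that 95% confidence intervals will be reported, without saying for which quantity.

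**The concern.** The target and the reported effect are on different scales. A chi-square test gives a p-value but no estimate or interval. The estimate that does come with an interval is a covariate-adjusted odds ratio from another model, and its translation into percentage points depends on the control-group rate. It is also conditional on the covariates, so it is not simply the odds ratio of the two-by-two table behind the primary test.

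What is at stake is how the result is read. The plan names 20 points as the improvement that matters. After the trial, readers will want to know whether the data support 20 points, rule it out, or do neither. That takes an interval for the difference, and in a trial of 131 the interval is wide enough to decide the answer.

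**Working it through.** **Inputs**
- Adherence 40% v 60%, and 131 patients at about 65 per group (Sample size); taken here as 65 and 66.
- Two-sided α = 0.05 (Sample size).
- 1:1 allocation (Randomization).
- No loss to follow-up assumed.

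**1. The plan's own figure.** The stated power is 80%. For a two-proportion test with pooled variance under the null and 65 per group:
- Null SE = √(2 × 0.25/65) = 0.0877
- Alternative SE = √(2 × 0.24/65) = 0.0859
- z = (0.20 − 1.96 × 0.0877)/0.0859 = 0.327, so power is about 63%

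The 80% is not reproduced; it would need 97 per group. That is a separate and larger issue in the same sentence. It matters here only because lower power makes an interval on the target scale more useful. The chi-square primary test does match the two-proportion test used for power, so the mismatch is confined to effect reporting.

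**2. The interval that is not planned.** Wald half-width for the difference:
- 1.96 × √(0.24/65 + 0.24/66) = 1.96 × 0.0856 = 0.168
- An observed 20 points would have a 95% CI of 20 ± 16.8, that is 3.2 to 36.8 points

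Treating the half-width as roughly constant, an observed difference between about 3.2 (20 − 16.8) and 16.8 points gives an interval containing both 0 and 20. A result there neither shows an effect nor excludes the target. The p-value and the two percentages do not by themselves make that visible.

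**3. What the odds ratio shows for the same data** (unadjusted, for comparison):
- OR = (0.60/0.40)/(0.40/0.60) = 2.25
- SE of log OR = √(1/(65 × 0.24) + 1/(66 × 0.24)) = √(1/15.6 + 1/15.84) = 0.357
- 95% CI = exp(0.811 ± 1.96 × 0.357) = 1.12 to 4.53

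**4. Translating an odds ratio of 2.25 into points.** With control rate p, the intervention rate is 2.25p/(1 − p + 2.25p).

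| Control rate | Intervention rate | Difference |
|---|---|---|
| 20% | 36.0% | 16.0 points |
| 40% | 60.0% | 20.0 points |
| 60% | 77.1% | 17.1 points |
| 80% | 90.0% | 10.0 points |

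The control rate is uncertain on the article's own figures. The Introduction gives Ethiopian non-adherence to inhaled therapies as 19.1% to 40.8%, which is 59.2% to 80.9% adherent, whereas the Sample size section assumes about 40% adherent. At 59.2% and 80.9%, the same odds ratio is 17.4 and 9.6 points.

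**The case against.** Several arguments on the other side are sound. The primary analysis compares two proportions, so the point difference follows by subtraction. The sentence on odds ratios comes straight after the logistic regression and can be read as describing that model's output; it does not exclude other measures. The Abstract promises 95% confidence intervals in general terms. An article may also leave further effect measures to a fuller plan.

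These arguments limit the point but do not remove it. The article does fix an effect measure, and it is on a different scale from its own target. The Abstract's sentence names no difference in proportions. A reader with counts could compute an interval, but that is no substitute for a prespecified estimate, and raw counts would not be enough if multiple imputation were used, which the plan allows when 5% or more of the data are missing.

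A reader might infer stronger versions that the documents do not support:
- That the trial was sized on 20 points. It was not: all eligible patients were taken, and the 20 points enter a post-hoc power statement.
- That the difference will never be estimated, or that odds ratios are all that will be shown. The two proportions give the point estimate; what is missing is its interval.
- That modelling non-adherence rather than adherence is itself a fault. The odds ratio and its interval simply invert, with the same p-value.
- That the adjusted model is demonstrably biased by too many parameters. The number of covariate categories is not given, and that is a different question from the effect scale.

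**Conclusion.** The point holds as a mismatch between the scale of the target and the scale of the named effect size. The article defines the meaningful effect as 20 percentage points, names an adjusted odds ratio from a model separate from the primary test, and plans no confidence interval for the difference. That interval is about ±17 points under the article's own 40% v 60% with 65 and 66 per group. The figure assumes complete follow-up; losses would widen it. An odds ratio of 2.25 is compatible with anything from 10 to 20 points over control rates of 20% to 80%, so it cannot replace the interval. Leaving baseline GMAS out of the adjusted model also gives up precision that data already being collected could provide. The primary test, sample size and power are untouched by this point. It should be corrected: it affects whether the result can be read against the trial's own target.

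**What to change.** In the Statistical analysis section:

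1. Name the difference in the proportion adherent at three months, with its 95% CI (for example Newcombe), as the primary effect estimate beside the chi-square test.
2. Add baseline GMAS to the adjusted logistic model for non-adherence, and report from it a standardised adjusted risk difference with a delta-method or bootstrap interval.
3. Keep the adjusted odds ratio as a secondary measure.

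The cost is modest: a few sentences in the plan and some extra analysis, mainly for the standardised difference and its interval. No new data or patients are needed. The Trial status section says that analysis has not begun and that no results have been examined, so the change can still be prespecified.
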